### Research questions

The following research questions are posed:Will music therapy (TMI) be as effective as standard treatment regarding the decrease of TSD symptoms (primary outcome) from pre to post treatment and from pre-treatment to 6 months’ follow-up?Will music therapy (TMI) be as effective as standard treatment regarding the decrease of dissociation and the improvement of attachment style and well-being (secondary outcomes) pre to post treatment and from pre-treatment to 6 months’ follow-up?Does any variable from the patient data at baseline (i.e., gender, age) specifically correlate with good outcomes of music therapy on trauma symptoms compared to standard treatment?Concerning patient satisfaction with therapy sessions, is there a difference between music therapy and verbal therapy, and is there any development in the assessment of the sessions during the therapy course?Will basic levels of salivary oxytocin, beta-endorphin and substance P be changed by the treatment, are any changes stable at follow-up, and are there differences between the two groups?Will the levels of salivary oxytocin, beta-endorphin and substance P be affected by one session, and are there a difference between the groups, and between a session at the beginning and in the end of treatment?

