#### Hypotheses

The hypotheses of the study are that music therapy (TMI) will not be less effective than verbal psychotherapy according to the principle of clinical equipoise, and that we will see a decrease in PTSD symptoms and dissociation as well as an increase of well-being and improvement of safe attachment style after both music therapy and standard treatment. Furthermore, we hypothesize that patient evaluation will be equally positive with regard to both treatment conditions. According to salivary hormones the hypotheses are, that music therapy will be no less effective than verbal therapy regarding increase of basic and session levels of oxytocin and decrease of basic and session levels of beta-endorphin and substance P.

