### Trial design

The research design is a randomized clinical trial with a parallel-group design including two intervention groups: music therapy (Trauma-focused Music and Imagery (TMI)) and standard psychological treatment. We use a non-inferiority framework, where we test whether or not music therapy is inferior to standard treatment. We intend to allocate 70 adult refugees diagnosed with PTSD. Repeated measures take place at baseline, post therapy and at 6 months’ follow-up. A short form of the primary outcome measure is also collected twice during the treatment period (session 5 and 10). Session evaluation from clients is collected after each session. Saliva samples are collected at baseline, post therapy and follow-up, and also pre and post sessions 4 and 14 (see the Standard Protocol Items: Recommendations for Interventional Trials (SPIRIT) flow chart; Fig. 1). All dimensions of the study protocol have been described adhering to the SPIRIT Checklist (Additional file 1). We also adhere to the revised Consolidated Standards of Reporting Trials (CONSORT) guidelines [63].

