At the end of each session a session evaluation is carried out. Music therapy patients are asked to what degree they have used the music method since their last session. All patients are asked to rate to what extent they feel understood and heard by the therapist (0–10) and how helpful they find the session (0–10) to be. They are also asked to name the most important themes of the session, and what they think they will remember/tell their spouse when returning home. The music therapists are collecting data about the use of music, intervention and themes of the session.

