#### Statistical methods

Statistical analysis will be carried out in the statistical environment R [82] in cooperation with the statistical department in the research unit of Region Zealand and PFI Region Zealand (Production, Research and Innovation Unit). Data will be treated according to the intention-to-treat principle. Analysis of all data will take place after the conclusion of data collection. Following the initial screening of the data significance tests concerning differences between standard treatment and music therapy will be carried out in order to assess the non-inferiority of music therapy. Significance and variance for the primary outcome measure will be calculated with analysis of covariance (ANCOVA), including data from five measuring points. Secondary questionnaire outcome data will also be calculated with ANCOVA, using three data points. Correlations between trauma symptoms, attachment, dissociation and demographic parameters are investigated. A regression analysis will be applied to look for predictors of improvement of trauma symptoms (HTQ) and change of attachment style, as well as predictors for improvement connected to treatment (music therapy or standard treatment). Analysis of hormones will be split up in an ANCOVA testing variance between groups and with time (baseline to follow-up), and simple significance tests of change after single sessions (between the third and 14th session and between the interventions). Session satisfaction data will be treated with descriptive statistical methods.

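### The session ratings carry a between-arm question, a time question and a hypothesis of equality, but the plan limits their analysis to descriptive methods

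*Protocol article*

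**What the plan says.** All the relevant text is in the protocol article.

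- **Research questions, fourth question**, on satisfaction with sessions: "is there a difference between music therapy and verbal therapy, and is there any development in the assessment of the sessions during the therapy course".
- **Hypotheses:** "we hypothesize that patient evaluation will be equally positive with regard to both treatment conditions". No margin is attached.
- **Trial design:** "Session evaluation from clients is collected after each session".
- **Secondary outcomes**, on content: "All patients are asked to rate to what extent they feel understood and heard by the therapist", scored 0–10. A second 0–10 item asks how helpful the session was.
- **Statistical methods**, the only statement on analysing these ratings: "Session satisfaction data will be treated with descriptive statistical methods".

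The same Statistical methods section gives the other outcomes more. For the scales it says: "Secondary questionnaire outcome data will also be calculated with ANCOVA, using three data points". For the salivary hormones, which the article calls exploratory, it plans comparisons between groups and over time.

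**The concern.** The fourth research question has two parts, a comparison between arms and a development over sessions, and the Hypotheses section adds a claim of equality. Each calls for an estimate and a statement of how precise it is. Descriptive methods need not supply either.

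What is at stake is how the result will be reported. If two sets of session means lie close together, the article's own hypothesis invites the conclusion that patients valued the treatments equally. If they lie apart, the research question invites the conclusion that one was preferred. With about 35 patients per arm, neither conclusion can be drawn from means alone. A non-significant difference test would not fill the gap either, because failing to find a difference does not show equality.

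**Working it through.** **Does another sentence cover these ratings?** The ANCOVA for secondary questionnaires uses three data points, which does not fit a rating taken at each of 16 sessions. The significance tests for non-inferiority are not tied to session ratings. So the descriptive sentence is the whole plan for them. It fixes a method, so this is not a detail left open for a separate analysis plan.

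**Is there a figure of the plan's own to reproduce?** Not on this point. The article gives no SD, margin or precision for session ratings, and its sample-size calculation concerns the HTQ only.

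**How wide would an interval be?**

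Inputs from the article:
- 35 patients per arm (Power calculation)
- 16 planned sessions, with 12 to 20 accepted (Dose)
- 0–10 scale (Secondary outcomes)

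Inputs assumed:
- SD of a single rating: 2 points
- within-patient correlation ρ: 0.3 to 0.7, the same for any two sessions
- every patient gives *m* = 16 ratings
- no clustering by therapist

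Formulas:
- variance of one patient's mean rating = SD² × (ρ + (1 − ρ)/*m*)
- 95% half-width for the arm difference = 1.96 × √(2 × variance / 35)

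| ρ | Variance of patient mean | Half-width (points) |
|---|---|---|
| 0.3 | 4 × (0.3 + 0.7/16) = 1.375 | 1.96 × √(2.75/35) = 0.55 |
| 0.5 | 4 × (0.5 + 0.5/16) = 2.125 | 1.96 × √(4.25/35) = 0.68 |
| 0.7 | 4 × (0.7 + 0.3/16) = 2.875 | 1.96 × √(5.75/35) = 0.79 |

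**How sensitive is this to the assumptions?**
- *Number of sessions.* With 12 ratings each the range is 0.56 (variance 4 × (0.3 + 0.7/12) = 1.433) to 0.80 (4 × (0.7 + 0.3/12) = 2.9). With 20 it is 0.54 (variance 1.34) to 0.79 (variance 2.86). The session count hardly matters.
- *SD.* The half-width is proportional to the SD. An SD of 1.5 gives 0.41 to 0.60, and an SD of 3 gives 0.82 to 1.19.
- *Patients.* With 32 per arm and an SD of 2, the range is 0.57 to 0.83.
- *A single session.* With 35 per arm and an SD of 2, the half-width is 1.96 × 2 × √(2/35) = 0.94 points. Session-by-session means are therefore less precise than the overall comparison.

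**What does this mean for a claim of equality?** Suppose, for illustration only, that a difference of up to 1 point were agreed to be unimportant. For the 95% interval to lie within ±1, the observed difference could be at most 1 − 0.55 = 0.45 points (ρ = 0.3) or 1 − 0.79 = 0.21 points (ρ = 0.7). Whether equality is supported thus depends on the interval and on a margin stated beforehand. The plan has neither.

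**The case against.** The strongest reply is that a descriptive analysis is a legitimate choice. The fourth research question, unlike the first two, is not labelled primary or secondary. Session evaluation also serves to monitor adherence (Procedures). A 70-patient trial that already tests the HTQ, several secondary scales and three neuropeptides has reason not to add more tests. This largely stands, and it is why the analysis should be supportive and not confirmatory. It does not remove the mismatch: if the ratings are to be described only, the hypothesis should say so.

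Three stronger readings are tempting, and the document does not support them.

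- *That the fourth question cannot be answered at all.* Means and plots by arm and session are descriptive methods and would answer it for the patients observed. What is missing is support for a conclusion beyond this sample, and above all for equality.
- *That the plan will overstate precision.* Treating all 2 × 35 × 16 = 1,120 ratings as independent would give a half-width of 1.96 × √(2 × 4/560) = 0.23, too narrow by a factor of about 2.3 to 3.4. The arithmetic is right, but no such pooled interval is planned.
- *That early stopping will push the session means upward over time.* This requires that those who stop rate sessions lower, which the article nowhere says. Risk of bias does warn of more dropout from standard treatment, but it does not link dropout to ratings. In the pilot, satisfaction was slightly higher towards the end although all 16 participants completed all sessions, so attrition did not cause that rise.

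It is also fair to say that a mixed model alone would not settle the matter. Without a margin, equality would still be judged by eye. A model with only a random intercept could give too narrow an interval for the slope difference if patients' trajectories vary. The four psychologists and four music therapists (Setting) may also induce clustering, particularly for the item about the therapist.

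**Conclusion.** The point holds in a limited form. The Research questions and Hypotheses sections ask more of the session ratings than the Statistical methods section provides. Descriptive summaries will describe this sample, but without an interval they support neither a difference nor equality between the arms. The uncertainty they would leave unstated is about ±0.55 to ±0.79 points for the mean arm difference. That range rests on an assumed SD of 2, an assumed within-patient correlation of 0.3 to 0.7, 35 patients per arm with 16 ratings each, and no therapist effect. None of the variability figures comes from the document.

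The severity is low. The ratings are not the primary outcome, and neither the sample size nor the HTQ non-inferiority conclusion depends on them.

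**What to change.** Replace the sentence on session satisfaction in Statistical methods with a linear mixed model for each of the two 0–10 ratings:

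- **Fixed effects:** arm, session number, arm-by-session interaction, location and gender.
- **Random effects:** patient intercept and patient slope for session.
- **Sensitivity analysis:** allowance for clustering by therapist.
- **Reporting:** the mean arm difference and the difference in slopes, each with a 95% confidence interval, labelled supportive and non-confirmatory. Summaries and plots by session can stay alongside.
- **Margin:** state, before the data are seen, the difference within which the ratings will be called equally positive, and use that wording only if the interval lies inside it.

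If no margin can be justified, restate the hypothesis on patient evaluation as a descriptive aim.

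The cost is a little more analysis work, with no new data and no change to trial conduct. The Blinding section says data stay concealed until the trial is complete, so the change can be specified before any results are known.

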#### Power calculation

In order to estimate the level of power we reviewed randomized and non-randomized trials where refugees suffering from PTSD were treated with stabilization and trauma exposure strategies with cognitive and narrative elements corresponding to the standard treatment in our study, and where the Harvard Trauma Questionnaire was used to measure changes in trauma symptoms (the primary outcome in the current study). The variations in the studies were considerable, and we chose to only look at studies that had a number of sessions that were similar to the current study, and where the mean baseline value of HTQ were around 3.3, a value that we found to correspond to our population in the pilot study [18, 62, 83–86]. Non-significant differences between 0.1 and 0.5 was found in HTQ from pre to post treatment. Based on our clinical experience and data from these studies, we estimate a clinical insignificant difference of 0.3 as the maximal difference between music therapy and standard treatment to confirm the non-inferiority hypothesis. A mean standard deviation of 0.48 on post-scores of HTQ was calculated from the studies referred above.

The power calculation was based on a significance level of 0.05, power 0.08, *d* = 0.3 and *SD* = 0.48. The calculation was carried out with software from Epi-info 7 (http://wwwn.cdc.gov/epiinfo/) in cooperation with Department for Statistics, Psychiatric Research Unit, Region Zealand and PFI.

The result indicates a minimum of 64 participants (32 in each group).

Adherence to music therapy has been found to be good in psychiatric patients with a low dropout rate (11.5%) [87]. In three former randomized clinical studies on psychological treatment of refugees with large samples low dropout rates (7–10%) were demonstrated at follow-up [21, 83, 88].

We have, therefore, chosen to include a dropout rate of 10% and thus end up with *n* = 70 (35 in each group).

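### Power is printed as 0.08 and the 0.05 level has no stated side; 64 participants matches power 0.80 only at a one-sided 5% level, and the analysis section does not name the interval to be set against 0.3

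*Protocol article*

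**What the plan says.** All points are in the protocol article.

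- **Framework** (Trial design): "We use a non-inferiority framework, where we test whether or not music therapy is inferior to standard treatment".
- **Margin** (Power calculation): "we estimate a clinical insignificant difference of 0.3 as the maximal difference between music therapy and standard treatment to confirm the non-inferiority hypothesis".
- **Variability** (Power calculation): "A mean standard deviation of 0.48 on post-scores of HTQ was calculated from the studies referred above".
- **Level and power** (Power calculation): "The power calculation was based on a significance level of 0.05, power 0.08". No side is given for the 0.05, and no true difference is stated.
- **Result** (Power calculation): "The result indicates a minimum of 64 participants (32 in each group"), after which the authors write that they have "chosen to include a dropout rate of 10% and thus end up with" 70, or 35 per group.
- **Analysis** (Statistical methods): "significance tests concerning differences between standard treatment and music therapy" are planned as the means of assessing non-inferiority, with ANCOVA for the primary outcome. The section gives no confidence level, no side for the test and no comparison with 0.3.

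**The concern.** Two figures that carry the design are in doubt. The printed power does not fit the printed sample size. The level that decides non-inferiority is left open, because 0.05 can mean a one-sided 5% test (upper limit of a 90% interval below 0.3) or a two-sided 5% level (upper limit of a 95% interval below 0.3).

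The two defects compound each other. Had power been printed correctly, a reader could work back from 32 per group to the side of the test. With 0.08 on the page that check is lost: one-sided 5% with 80% power and two-sided 5% with 70% power both round up to 32.

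What is at stake is the primary conclusion. If the level is still open when the data are seen, some results would count as non-inferior under one interval and not under the other.

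**Working it through.** **Inputs**, all from Power calculation: margin 0.3; SD 0.48; level 0.05; power printed as 0.08; 32 per group; 10% dropout; 70 randomised. Assumption, not stated in the article: true difference 0.

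**Formula** (normal approximation, equal groups): n per group = 2 × (z_level + z_power)² × (0.48/0.3)². Since (0.48/0.3)² = 2.56, the multiplier is 5.12.

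**Step 1. Reproduce the stated 32 per group.** One-sided 5%, power 0.80: (1.645 + 0.842)² × 5.12 = 31.65, so 32 per group and 64 in total. This matches.

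**Step 2. Take the printed power literally.** One-sided 5%, power 0.08: 0.29, so 1 per group. Two-sided 5%, power 0.08: 1.58, so 2 per group. Neither is near 32, so 0.08 was not the value used.

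**Step 3. Try other readings of the level.**

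| Reading | n before rounding | Per group |
|---|---|---|
| One-sided 5%, power 0.80 | 31.65 | 32 |
| One-sided 2.5% (95% interval), power 0.80 | 40.19 | 41 |
| One-sided 2.5% (95% interval), power 0.70 | (1.960 + 0.524)² × 5.12 = 31.6 | 32 |
| Equivalence, two one-sided 5% tests, power 0.80 | 43.85 | 44 |

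Among these readings at power 0.80, only the one-sided 5% level gives 64.

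**Step 4. Power at 32 per group.** Standard error of the difference = 0.48 × √(2/32) = 0.12, and 0.3/0.12 = 2.5.

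- One-sided 5%: Φ(2.5 − 1.645) = 80.4% (79.6% with the noncentral t).
- One-sided 2.5%: Φ(2.5 − 1.960) = 70.5% (69.2% with the noncentral t).

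**Step 5. What the choice means for the result.** At 32 per group and SD 0.48, the upper limit is the observed difference plus 1.645 × 0.12 = 0.197 (90% interval) or plus 1.960 × 0.12 = 0.235 (95% interval). Non-inferiority therefore needs an observed difference below 0.103 or below 0.065 respectively. Between those values the verdict depends on a level the article does not state.

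**Step 6. Dropout.** 64 × 1.1 = 70.4, close to the stated 70. But 70 × 0.9 = 63, one below the stated minimum; 64/0.9 = 71.1, or 72 for equal groups. At 63 evaluable (31.5 per group) power is 79.8% one-sided 5% and 69.9% one-sided 2.5%.

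**The case against.** The strongest reply is that nothing in the sizing fails once an obvious misprint is corrected. With 0.80 in place of 0.08, the article's own margin, SD and level give its own 64 under a one-sided test, which is the natural form for the framework it declares. The sentence on significance tests also goes on to say that they serve to assess non-inferiority, so it does not contradict a one-sided level. No section mentions a two-sided test or a 95% interval, and the interval may be fixed in a full protocol or analysis plan that is not shown. All of this stands. It rules out two inferences a reader might draw: that the stated figures do not describe the design, and that the one-sided level was concealed. The side is simply unstated.

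The second reply is that the 70% figure belongs to an unadjusted comparison of post-treatment scores, while the primary analysis is ANCOVA. If that adjusts for baseline, the residual variance falls by a factor of about 1 − ρ², where ρ is the correlation between baseline and post-treatment scores. The article gives no ρ and does not list the covariates. Purely as an assumed range, at 63 evaluable and one-sided 2.5%, power would be about 74% for ρ = 0.3, 82% for ρ = 0.5 and 87% for ρ = 0.6, reaching 80% near ρ = 0.46. This also stands: a reader might infer that the trial is underpowered if a 95% interval is used, but the article does not establish that.

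The third reply is that the dropout step is immaterial. It is: one evaluable participant, and 80.4% against 79.8%.

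What the replies do not remove is that the printed power is wrong and that the one section which sets out the sizing assumptions leaves the deciding level ambiguous. The Statistical methods section does not resolve it.

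**Conclusion.** The point holds in a limited form. The printed power of 0.08 is inconsistent with 32 per group; the value that fits is 0.80, with a one-sided 5% level and a true difference of 0. The side of the level is not stated, and the planned tests of differences are tied neither to the 0.3 margin nor to an interval.

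The size of the ambiguity is 32 against 41 per group, or about 80% against about 70% unadjusted power at 32 per group. These figures rest on SD 0.48, margin 0.3, true difference 0 and the normal approximation, before any gain from covariate adjustment. The dropout shortfall deserves a note only.

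**What to change.** 1. In Power calculation, print power as 0.80 and state the assumed true difference.
2. Have the sponsor confirm the level used for sizing and state it. One-sided 0.05 is the one that reproduces 64, but the article does not say so and the sponsor should not have it written in unconfirmed.
3. In Statistical methods, define the primary non-inferiority conclusion by the upper limit of the matching interval against 0.3: a two-sided 90% interval if the level is one-sided 0.05.
4. If a 95% interval is intended, restate the power as about 70% before covariate adjustment. Holding 80% unadjusted would take 41 per group.
5. State the evaluable number after 10% dropout as 63, with power about 79.8% at one-sided 5%.

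The cost is a few corrected figures and one added sentence in the analysis section, with no change to enrolment. The price is openness: either a 90% interval is declared as the deciding one, or a lower unadjusted power is put on record. This should be settled before the outcome data are opened.

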#### Randomization

Randomization is carried out with the help of the randomization software Sealed Envelope (https://sealedenvelope.com/). Stratification is applied regarding geography (three different locations) and gender (male/female). Within the strata, random permuted blocks of even length (blocks of four or six participants) are used. When a participant has given informed consent and completed baseline measures with one of the three music therapists who takes care of the research procedures (one in each location), the music therapist/researcher logs on to the randomization website and types patient ID number, gender and location. Information of the treatment group is provided immediately on the website and is also sent by email to the researcher. The status of the patient is typed into the Xpsy database, and the patient is referred to either music therapy or standard treatment at the location.

